### Outcomes

The primary objective is to assess the impact of the intervention on functionality, as measured by the GAS [26,27,33], which evaluates the extent to which participants achieve their individual goals. The secondary objective is to evaluate problem-solving and reasoning skills using the maze score from the MATRICS assessment [28]. An exploratory analysis will also examine changes in PANSS scores and other domains of the MATRICS assessment. All assessments will be conducted at the end of the 10-week intervention period and during the 6-month follow-up period.

### Clinical Assessments

To evaluate clinical symptomatology, the PANSS will be used [34]. PANSS is a widely used instrument consisting of 30 items and is used to measure the severity of clinical symptoms in patients with schizophrenia. The interviewee psychiatrist is rated on a scale of 1 to 7 by the interviewer psychiatrist.

### Functionality Assessments

The GAS is a type of assessment that is centered on personal goals and is commonly used in physical rehabilitation (lifestyle, type of handicap, and aspirations) but is not often used in psychiatry [26,27]. GAS was first used in mental health settings in the 1960s and has also been applied for cognitive rehabilitation [33,35].

The patient and interviewer work together to define individual goals that are specific, measurable, attainable, realistic, and timely, using the “SMART” method. These goals are based on the patient’s current lifestyle, daily routines, interests, and needs. If a patient expresses a desire for a long-term goal that cannot be achieved in a short time, the interviewer helps the patient break it down into smaller achievable goals that fit within a defined time frame. The GAS score is based on a defined goal and considers its weightage. Achievement of the defined goal is typically scored as 0, and if the achievement is better or worse than that defined, the score is either +1 or +2 or 1 or 2, respectively. The patient also rates the importance and difficulty of each goal on a 0-3 Likert scale. The final score is calculated by an algorithm that provides a baseline score, an achieved score, and the difference between the two [27].

### Cognitive Assessments

The estimated IQ (for inclusion criteria) will be assessed using 2 subtests from the Brazilian version of the Wechsler Intelligence Scale [36], which are vocabulary and rational reasoning.

To assess cognitive changes, 9 tests from the Brazilian version of the MATRICS [28,37] will be used. The test evaluates 7 cognitive domains:

Speed of processing: Trail Making Test, Brief Assessment of Cognition in Schizophrenia Symbol Coding, and Category Fluency Animal Naming TestAttention: Continuous Performance Test-Identical PairsWorking memory: Spatial Span and Letter-Number Span TestVerbal learning: Hopkins Verbal Learning Test-RevisedVisual learning: Brief Visuospatial Memory Test-Revised.Reasoning and problem-solving: neuropsychological assessment battery maze.

The Mayer-Salovey-Caruso Emotional Intelligence Test Managing Emotions subtest was excluded due to its low-reliability coefficient in Brazilian versions [28].

### Power and Sample Size

Sample calculation was performed using G*Power software (Heinrich-Heine-University), considering a post hoc analysis for 17 participants, effect size (Cohen *d*=0.5) [25], and estimated power (β=.62), where the GAS score means will be compared pre- and post-FIE intervention (described in the Intervention section) using a matched pairs Student *t* test.

### Analysis

Data will be analyzed using IBM SPSS (version 21) or Jamovi software following the intention-to-treat approach. The last observation carried forward will be the procedure to impute the missing data. Sociodemographic and baseline information of the patients will be described to show the sample characteristics.

The study will use ANOVA or Kruskal-Wallis tests to analyze changes in numerical variables, including primary and secondary outcomes, as well as exploratory analyses, depending on the data distribution. Post hoc pairwise comparisons will be conducted using the Bonferroni adjustment for multiple comparisons in the Friedman test. The chi-square test will be used to analyze categorical data, such as sex. The effect size will be calculated using Cohen *d*, based on the mean and SD of the mean t1 for the GAS.

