## Methods

### Research Design

The proposed research design is an open-label interventional pilot study that aims to investigate the effects of the FIE program on the functionality of patients with FES based on their personal goals. The study will measure outcomes at 3 time points that are baseline (t0), after the intervention (t1), and at the 6-month follow-up (t2).

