**Figure 1 figure1:**
[figure not shown]
Study design and patient flowchart. (1) We applied the informed consent form, IQ assessment, and Structured Clinical Interview for DSM-5-Research Version. (2) Participants who are deemed ineligible or unwilling to participate or continue in this study will be removed from the study. (3) We conducted baseline assessments using Measurement and Treatment Research to Improve Cognition in Schizophrenia (MATRICS), Positive and Negative Syndrome Scale, and Goal Achievement Scale. (4) We are awaiting a group of 2-3 eligible participants who have successfully completed the IQ and MATRICS assessments. (5) A 10-week training program with Feuerstein Instrumental Enrichment (FIE) will be conducted, with a frequency of 2 sessions per week. (6) A postintervention assessment will be conducted 1 week after the completion of the FIE program. (7) A follow-up assessment will be conducted 6 months after the completion of the FIE program. (8) The primary outcome of the study will be functionality, which will be measured using the Goal Attainment Scale scores. In addition, problem-solving and reasoning abilities will be assessed using the maze scores from the MATRICS assessment.

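### Last observation carried forward sets a missing 6-month score equal to the post-training score, so part of any 6-month maintenance result is assumed

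*Protocol article*

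**What the plan says.** The Analysis section states that data will be analysed "following the intention-to-treat approach" and then gives the imputation rule: "The last observation carried forward will be the procedure to impute the missing data". The rule is not limited to one outcome or visit, and the article names no other method for missing data.

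Research Design lists three time points: t0, t1 and t2. The Figure 1 legend gives the timing of the last two: "A postintervention assessment will be conducted 1 week after the completion of the FIE program" and "A follow-up assessment will be conducted 6 months after the completion of the FIE program". Under Outcomes, the Goal Achievement Scale (GAS), the maze score, the PANSS and the other MATRICS domains share this schedule: "All assessments will be conducted at the end of the 10-week intervention period and during the 6-month follow-up period".

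There is one arm and no control group (Limitations). The power statement concerns the pre-post GAS comparison in 17 participants. No dropout rate is assumed. Limitations reports no dropouts among the 11 enrolled so far.

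**The concern.** With only three visits, the value carried into a missing t2 is the t1 score, taken 1 week after training. The imputed change from t1 to t2 is zero by construction. A participant lost between t1 and t2 is thus entered as having kept all of any gain made by t1. Whether a gain lasts 6 months is a question the t2 data can answer, and the rule answers part of it by assumption. There is no control arm that might reveal or offset this.

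For a missing t1 the carried value is baseline, so the GAS change is set to zero. If the participant would have improved, this pulls the primary pre-post change towards zero. The rule therefore acts in different directions at the two visits, and in both cases an imputed value is analysed as if it had been observed.

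**Working it through.** **Inputs from the article.** n = 17; a pre-post effect of Cohen d = 0.5 (Power and Sample Size); visits t0, t1 and t2; last observation carried forward (LOCF) as the missing-data rule.

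**Assumed inputs.** The number missing at t2, the share of gain retained, and the correlation between visits. The article gives none of these.

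**The plan's own figure.** The only related calculation is the power of 0.62 (printed as β) for the paired t test. With 16 degrees of freedom and noncentrality 0.5 × √17 = 2.06, a one-sided 5% test has power 0.629, close to the stated value; a two-sided 5% test has 0.491. This confirms n and d as inputs but does not bear on the missing-data rule.

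**Step 1: bias at t2.** Let G be the mean gain at t1, R the share of it truly retained at t2, and m the number seen at t1 but not at t2. Suppose G and R are equal in leavers and completers.

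- True mean change at t2: R·G
- LOCF mean change: [(n − m)·R·G + m·G]/n = G·[R + (1 − R)·m/n]
- Bias: (m/n)·(1 − R)·G, the share missing times the gain lost since t1

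With R = 50%:

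- m = 3: (14 × 0.5 + 3)/17 = 10/17 = 59%
- m = 6: (11 × 0.5 + 6)/17 = 11.5/17 = 68%

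With m = 0 or R = 100% the bias is zero.

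**Step 2: intervals.** A simulation used 20,000 runs per scenario, n = 17, SD 1 at each visit, pairwise correlation 0.5 (so the SD of a change is 1) and a t1 gain of 0.5. t2 was missing completely at random in 10%, 20% or 30%. Paired t intervals were used. Entries are the mean LOCF estimate, with 95% interval coverage in brackets.

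| Gain lost by t2 | Contrast (true value) | 10% missing | 20% missing | 30% missing |
|---|---|---|---|---|
| None | t2−t0 (0.50) | 0.503 (0.949) | 0.498 (0.949) | 0.499 (0.951) |
| None | t2−t1 (0) | 0.002 (0.950) | 0.002 (0.950) | 0.001 (0.952) |
| Half | t2−t0 (0.25) | 0.278 (0.949) | 0.300 (0.947) | 0.325 (0.941) |
| Half | t2−t1 (−0.25) | −0.224 (0.950) | −0.200 (0.940) | −0.176 (0.927) |
| All | t2−t0 (0) | 0.051 (0.945) | 0.100 (0.934) | 0.150 (0.912) |
| All | t2−t1 (−0.50) | −0.448 (0.946) | −0.397 (0.915) | −0.349 (0.869) |

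When all the gain is lost, the two-sided 5% test of t2−t0 rejects in 5.5%, 6.6% and 8.8% of runs. Observed pairs alone were unbiased in every scenario, with coverage from 0.947 to 0.953.

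With no gain lost, the LOCF standard error for t2−t0 is 0.239 at every missing rate, against 0.252, 0.267 and 0.286 for observed pairs. For t2−t1 it is 0.225, 0.212 and 0.198, against 0.251, 0.266 and 0.286. The LOCF interval for t2−t1 thus narrows as more data are lost. Once gain is lost, it is also centred on a shifted value, and coverage falls.

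**The case against.** The strongest reply is that the damage is confined and conditional. The power statement and the planned effect size both concern GAS at t1, and there a missing value becomes baseline, which works against the hypothesis if leavers would have gained. None of the 11 enrolled had dropped out, and with complete t2 data the rule does nothing. Under-coverage is modest unless much gain is lost and many t2 scores are missing: even with all the gain lost, t2−t0 coverage is 0.945 at 10% missing. All of this stands, except that the dropout report does not say how many of the 11 had reached t2.

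Four stronger readings are tempting and are not supported.

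- A reader might infer that standard errors and p-values are wrong in general. In the simulation, coverage stays near 0.95 when no gain is lost.
- A reader might infer that those who leave are those who relapsed. Nothing in the article shows this for this trial. It would also undercut the equal-retention illustration and the mixed model. If 14 completers kept 50% and 3 leavers kept none, true retention would be 7/17 = 41%. LOCF would still report 59%, and a mixed model about 50% if the leavers' t0 and t1 scores resembled the completers'.
- A reader might take 6 missing t2 scores as the expected case. Six participants were still to be enrolled in February 2024 and analysis is planned to end in September 2024, while training plus follow-up lasts 10 weeks and 6 months. Their t2 visits would fall after that window. The article does not say that visits not yet due would be imputed, so 6 remains an illustration.
- A reader might infer that the article derives LOCF from intention-to-treat, or that t2 serves only to show maintenance. It states the two analysis rules in separate sentences and lists t2 simply as a time point for all assessments.

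**Conclusion.** The point holds for t2. For every participant seen at t1 but not at t2, the stated rule fixes the later change at zero and so overstates retention whenever gain is lost. The mechanism follows directly from the rule and the visit schedule. Its size does not: the 59% and 68% figures rest on assumed numbers missing and on 50% retention that is equal in leavers and completers. The coverage figures rest on missingness completely at random and a correlation of 0.5. If no t2 is missing or no gain is lost after t1, there is no material harm. The effect on the primary pre-post comparison is probably small and towards zero. This is a worthwhile and inexpensive improvement to the plan; it does not threaten the primary analysis.

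**What to change.** Replace LOCF as the main rule with a likelihood-based linear mixed model on all observed t0, t1 and t2 values, with time as a category and a random patient effect, keeping every participant who started training. This keeps the intention-to-treat set without filling in scores. If the data call for the rank-based option in the Analysis section, analyse observed pairs without carried-forward values.

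Report LOCF and a pessimistic value for missing t2, for example return to baseline, only as sensitivity analyses. They are needed because missing at random may not hold. Return to baseline is itself a single imputation, so it shows how far the result could move and is not a better estimate. Do not base a claim of 6-month maintenance on LOCF alone.

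The cost is a change of main model from the planned ANOVA, reliance on missing at random, a little more analysis work and slightly wider intervals. As a guide, at 20% missing the t2−t0 standard error in the simulation was 0.267 for observed pairs against 0.239 under LOCF.

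### The stated power of .62 belongs to a single unadjusted paired t test at an undeclared level, but the Analysis section plans a three-time-point test in which that contrast is only a post hoc comparison

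*Protocol article*

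**What the plan says.** Three sections of the protocol article bear on the test of the primary outcome.

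- **Power and Sample Size.** The calculation is described as "considering a post hoc analysis for 17 participants", with "effect size (Cohen *d*=0.5" and "estimated power (β=.62". It concerns one comparison, "where the GAS score means will be compared pre- and post-FIE intervention", made "using a matched pairs Student *t* test". Neither a significance level nor a sidedness is given here or elsewhere.
- **Research Design.** "The study will measure outcomes at 3 time points": baseline (t0), after the intervention (t1) and the 6-month follow-up (t2).
- **Analysis.** Changes in the primary, secondary and exploratory numerical outcomes go to ANOVA or Kruskal-Wallis, "depending on the data distribution". The only multiplicity rule follows: "Post hoc pairwise comparisons will be conducted using the Bonferroni adjustment for multiple comparisons in the Friedman test". The matched-pairs t test is not mentioned in this section.

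**The concern.** The comparison that was powered and the analysis that is planned are not the same. Three time points give three pairwise contrasts. The powered one, t0 versus t1, has no separate standing in the Analysis section and can be reached only as a post hoc comparison. The one adjustment that is stated belongs to the Friedman test, which is not among the omnibus tests offered. Kruskal-Wallis, which is offered, is a test for independent groups, whereas here the same patients are measured three times.

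The t0-t1 change in GAS carries the main hypothesis in an uncontrolled study of 17 people. Its test and its threshold should not be open to choice once the data have been seen. If the Bonferroni rule does apply to it, power is spent on protecting two follow-up contrasts that the sample-size section never treats as primary, and the published power figure does not describe the test that will be reported.

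**Working it through.** **Inputs.** From Power and Sample Size: n = 17, d = 0.5 (read as the standardised mean of the paired differences, the effect size for a matched-pairs test), stated power .62. From Research Design: 3 time points. Alpha is not stated, so 0.05 is assumed and other values are tried below. Sidedness is not stated, so both are shown.

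**Formula.** A paired t test with n pairs has df = n − 1 = 16 and noncentrality d√n = 0.5 × √17 = 2.06. Power is the probability that a noncentral t variable with these parameters exceeds the critical value (for a two-sided test, plus the negligible lower tail).

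**Step 1: reproduce the plan's figure.**

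| Test | Critical t (16 df) | Power |
|---|---|---|
| one-sided 0.05 | 1.746 | 0.629 |
| two-sided 0.10 | 1.746 | 0.629 |
| two-sided 0.05 | 2.120 | 0.491 |

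The stated .62 agrees with the first two rows (0.6287 cut to two decimals) and is 13 points above the third (0.62 − 0.49). The figure is printed with the symbol β but described as power. Read literally as a type II error it would mean power of 0.38. The nearest variant tried, two-sided 0.025, has type II error 0.633, which does not match .62 to two decimals, and nothing in the plan points to that level.

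**Step 2: power on the adjusted route.** Three time points give 3 × 2 / 2 = 3 contrasts, so Bonferroni gives 0.05 / 3 = 0.0167 for each.

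| Test | Critical t (16 df) | Power | Stated .62 minus this |
|---|---|---|---|
| one-sided 0.0167 | 2.328 | 0.416 | about 20 points |
| two-sided 0.0167 | 2.673 | 0.303 | about 32 points |

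**Step 3: rank-based check.** The adjusted route is a rank test, so the paired-t values in step 2 only stand in for it. Simulation with normal data, n = 17 and d = 0.5 gave these two-sided results:

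- Wilcoxon signed-rank: 0.46 at 0.05 and 0.27 at 0.0167.
- Friedman rank-sum contrast with Bonferroni: about 0.26 (assuming correlation 0.5 between visits and the gain held at t2).

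Under these assumptions the rank route is somewhat weaker than step 2 shows.

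**Step 4: sample size for the same target.** With a two-sided paired t test and d = 0.5, 62% power needs 23 participants at 0.05 and 33 at 0.0167. The plan has 17.

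**The case against.** The best defence of the plan has four parts.

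1. **The .62 is not a miscalculation.** A reader might infer from the two-sided 0.49 that the figure is simply wrong. The documents do not support that. It reproduces at one-sided 0.05, the hypothesis is worded as an improvement, and two-sided testing is nowhere promised. This stands. The fault is that level and sidedness are undeclared.

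2. **The threshold is not shown to switch between 0.05 and 0.017.** A reader might infer that the primary contrast is tested at one or the other depending on a distribution check. No alpha is stated, so both values are assumptions. The text is silent about post hoc comparisons after ANOVA and does not say they are unadjusted; a full analysis plan could fill that gap. This stands too. What is established is that a rule is stated for one route only.

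3. **The omnibus step may matter.** If post hoc contrasts follow only a significant omnibus test, an unadjusted t0-t1 contrast would not have power 0.49. Simulation with n = 17, normal data, correlation 0.5 and omnibus level 0.05 gave about 0.38 to 0.41 across three patterns at t2, against about 0.29 on the adjusted route. The gap between routes is then about 9 to 12 points, not the 19 that 0.49 − 0.30 suggests. This weakens any claim about the exact cost of the adjustment. It does not bring either route closer to .62.

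4. **The sample-size section already names the paired test.** It does, and if that test governs, the power figure can stand as one-sided. But the Analysis section expressly covers the primary outcome and assigns it a different test. The article does not say which section prevails.

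This is also a pilot with no decision tied to a p-value, which limits the consequences but does not remove the inconsistency.

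**Conclusion.** The point holds in this form. The stated power describes one unadjusted paired t test at one-sided 0.05 (equivalently two-sided 0.10), and the Analysis section does not plan that test for the primary outcome. On the only adjusted route that section describes, .62 is not delivered under either sidedness: about 0.42 one-sided or 0.30 two-sided by the paired-t calculation, and about 0.26 to 0.27 two-sided in the rank-based simulations. Without adjustment, power is 0.63 one-sided or 0.49 two-sided.

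These values rest on an assumed alpha of 0.05, on d = 0.5 read as a paired effect size, on all three pairwise contrasts being counted, and on 17 analysed participants. The simulated values also assume normal data. Separately, and without any assumption about alpha, Kruskal-Wallis and Friedman are named inconsistently for the same repeated-measures data, and Kruskal-Wallis does not suit that design.

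**What to change.** In **Analysis**:

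- Name the t0-t1 GAS paired comparison as the single primary test, made once and without Bonferroni. If a rank-based alternative is kept for it, use the same significance level.
- Treat t0-t2 and t1-t2 as secondary, with the same adjustment on the parametric and the rank-based path.
- Replace Kruskal-Wallis with Friedman throughout for the three-time-point rank analysis.

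In **Power and Sample Size**:

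- State alpha and sidedness, and label the figure as power rather than β.
- Restate power for that one test: 0.49 for two-sided 0.05, or 0.63 if one-sided 0.05 is declared.

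The cost is a few sentences and, if the test is two-sided, a less favourable power figure. No new data or patients are needed.

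### On the rank path, the stated Friedman pairwise comparison makes the pre-post GAS result depend partly on the 6-month scores, although the question posed involves two visits only

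*Protocol article*

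**What the plan says.** The protocol article sets three visits: baseline (t0), after training (t1) and 6 months later (t2). Under Outcomes it states: "All assessments will be conducted at the end of the 10-week intervention period and during the 6-month follow-up period". GAS and the maze score are therefore measured at t2 as well as t1.

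The Power and Sample Size section describes a two-visit comparison: "GAS score means will be compared pre- and post-FIE intervention", by a matched-pairs t test with 17 participants and Cohen d of 0.5.

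The Analysis section describes something else: "The study will use ANOVA or Kruskal-Wallis tests to analyze changes in numerical variables, including primary and secondary outcomes", the choice between the two being made "depending on the data distribution". It then adds: "Post hoc pairwise comparisons will be conducted using the Bonferroni adjustment for multiple comparisons in the Friedman test". On missing data it says: "The last observation carried forward will be the procedure to impute the missing data". It names no separate two-visit rank test for t0 against t1.

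**The concern.** A pairwise comparison made within the Friedman test ranks each patient's three visits together and compares mean ranks. The t0-t1 statistic is then not a function of t0 and t1 alone. A t2 score that falls between a patient's t0 and t1 widens their rank gap from 1 to 2. A t2 score outside both leaves the gap at 1.

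The post-training answer on the primary outcome can therefore change with scores collected 6 months later, while the t0 and t1 data stay the same. This holds at any alpha. It also holds if Kruskal-Wallis, which is a test for independent groups, is replaced by Friedman as the omnibus rank test. The rank path is a real prospect with 17 patients and a GAS score built from five-level goal ratings (Functionality Assessments section).

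**Working it through.** **1. The plan's own figure.** Inputs from Power and Sample Size: n=17, d=0.5, matched-pairs t test, stated power 0.62 (printed as β). No alpha is given, so 0.05 is assumed. With a noncentral t, df=16 and noncentrality 0.5 × √17 = 2.06, power is 0.629 one-sided and 0.491 two-sided. The stated figure is matched by the one-sided test. Either way it refers to a test that uses t0 and t1 only.

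**2. The Friedman pairwise statistic.** With k=3 visits and n=17:

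z = (mean rank t1 − mean rank t0) / √(k(k+1)/(6n)), where √(12/102) = 0.343.

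Bonferroni over three pairs multiplies p by 3 (per-pair level 0.05/3 = 0.0167, critical z = 2.394).

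**3. Fixed t0 and t1, only t2 moved** (constructed example). Thirteen patients gain 1 unit from t0 to t1 and four lose 1 unit.

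| t2 in every patient | Mean ranks t0, t1, t2 | z | Adjusted p |
|---|---|---|---|
| t1 − 0.1 | 25/17=1.47, 47/17=2.76, 30/17=1.76 | 3.77 | 0.0005 |
| t1 + 0.1 | 25/17=1.47, 30/17=1.76, 47/17=2.76 | 0.86 | 1.0 |
| t1 exactly (all filled by LOCF) | 1.47, 2.26, 2.26 | 2.32 | 0.062 |

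The last row uses the untied standard error. Ranks 1, 2.5, 2.5 have a sum of squared deviations of 1.5 instead of 2, so the tie correction multiplies the SE by √0.75. That gives z = 2.67 and adjusted p = 0.023. A Conover-type comparison behaves the same way: adjusted p is 0.0001 in the first row and 0.80 in the second.

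Any test on t1 − t0 alone gives one answer for all three rows. With equal-sized changes the exact signed-rank test reduces to the sign test: p = 0.049, or 3 × 0.049 = 0.147 after Bonferroni.

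**4. How often it matters.** Simulation with n=17, t1 − t0 normal with SD 1 and mean 0.5 or 0, and t2 = t1 + drift + normal noise of SD s. The values of drift and s are assumptions. The nominal rate of a false gain is 0.0167/2 = 0.8%.

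| s (SD of t1-t2 change) | Power at d=0.5, drift −0.3 | Power at d=0.5, drift +0.3 | False gain, drift −0.3 |
|---|---|---|---|
| 0.3 | about 52% | about 6% | about 5% |
| 0.5 | about 37% | about 11% | 2.4% |
| 1.0 | about 22% | about 14% | 0.8% |
| Exchangeable model (equal correlations, SD of every change 1) | 26% | 22% | 0.9% |

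At s=0.3 with no drift, power is 26%. The exact signed-rank test on t1 − t0 at the same 0.0167 level has about 28% power and a 0.7% to 0.8% false-gain rate in every row. Durbin-Conover comparisons at s=0.3 give 54%, 27% and 16% power for drift −0.3, 0 and +0.3, and 6.3% false gain.

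**5. LOCF.** With 4 of 17 t2 values copied from t1 (drift −0.3, s=0.3), power is about 45% and false gain 3.9%. In that setting LOCF dilutes the distortion. The Limitations section reports no dropouts among the 11 participants enrolled so far.

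**The case against.** - **The sentence may mean something else.** If the authors intend Bonferroni-adjusted signed-rank tests on each pair after a Friedman test, t2 never enters the t0-t1 statistic and the point falls away. That is possible, but the text places the comparisons in the Friedman test and names no other. The point rests on the literal reading.
- **Only one branch is affected, and that paragraph is already inconsistent.** It names Kruskal-Wallis and then Friedman, and the power section names a paired t test. This stands. However, correcting Kruskal-Wallis to Friedman alone would leave the dependence on t2 in place.
- **The large effects need a particular pattern.** They require 6-month changes far less variable than the 10-week changes, and the simulations draw normal data, which might not lead to the rank path at all. This stands, and it limits the size.
- **Mean-rank follow-up is a recognised method, and this is a small open-label pilot without a control group.** True, but it answers a three-visit question and the plan's stated question has two visits.

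Three stronger readings are tempting. A reader might infer that the t0-t1 error rate is uncontrolled in general. It is not: at SD 1.0, or under the exchangeable model, it is about nominal. A reader might infer that LOCF alone decides the result. The tie-corrected p of 0.023 and the absence of dropouts so far do not support that. A reader might also take the fixed example as a true gain being hidden. The proposed test is itself not significant there after Bonferroni (0.147), so the example shows only that the Friedman comparison depends on t2.

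**Conclusion.** The point holds for the rank path, on the literal reading of the pairwise sentence. The t0-t1 comparison of GAS and maze then depends partly on t2, which does not match the two-visit question in the power section.

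How much this matters turns on t2 behaviour that the protocol does not inform. The effect is serious if t2 follows t1 closely with a small common drift, and small if t1-t2 changes vary as much as t0-t1 changes. Drift and its SD are assumptions throughout, as are a two-sided 0.05 level and Bonferroni over three pairs. LOCF is a minor contributor. The point is worth correcting because the remedy is cheap and removes the dependence whatever t2 does.

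**What to change.** In the Analysis section, replace the Friedman pairwise comparisons for GAS and maze. State that on the rank path t0-t1 is tested with the exact Wilcoxon signed-rank test on each patient's own t1 − t0 change, reported with the Hodges-Lehmann median change, and that t0-t2 is tested separately in the same way on t2 − t0. Apply whatever multiplicity rule is adopted to those p values. Keep Friedman, if wanted, only as a descriptive test over the three visits. This is the rank counterpart of the matched-pairs t test in the Power and Sample Size section.

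The cost is one sentence and no new data. The downside is that the signed-rank test assumes roughly symmetric changes and drops patients whose change is exactly zero, which can happen with a GAS score built from a few levels.

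### The Cohen d rule for the primary outcome names the t1 GAS mean and SD but neither baseline nor change, so as written it does not measure the pre-post effect

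*Protocol article*

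**What the plan says.** The only effect-size rule is the last sentence of the Analysis section, which has Cohen d "based on the mean and SD of the mean t1 for the GAS". Three other places show what the effect ought to be.

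- **Abstract, Methods:** the primary outcome is the change in GAS.
- **Functionality Assessments:** the GAS score comes from "an algorithm that provides a baseline score, an achieved score, and the difference between the two", so each patient has a change value. The same section says that meeting the defined goal is usually scored 0.
- **Power and Sample Size:** the calculation is described as "considering a post hoc analysis for 17 participants", with Cohen d = 0.5 and a figure of 0.62 labelled β. It is a comparison "where the GAS score means will be compared pre- and post-FIE intervention", made "using a matched pairs Student *t* test".

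**The concern.** The outcome is a change, and the planning value is a standardized change. The rule for reporting the effect mentions only the time point after the intervention. A mean at one time divided by its own SD says how far the group lies from the zero of the scale. It can be large when nothing changed, and it can be zero when patients improved. The phrase for the denominator is also unclear: an SD of scores and an SD of a mean (a standard error) are different quantities.

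This matters more than usual because the study is a single-arm pilot of 17 patients with a stated power of 0.62. A significance test will carry limited information, and a later trial would take its planning value from the effect size. A d that leaves out baseline cannot show a gain in functionality and cannot be set against the 0.5 assumed here.

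**Working it through.** **Inputs.** From Power and Sample Size: n = 17, d = 0.5, stated power 0.62, paired t test. The document gives no alpha, sidedness, GAS mean, GAS SD or pre-post correlation. Values used for these below are assumptions.

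**1. What kind of d is the planning value?** For a paired t test, df = 16 and the noncentrality is 0.5 × sqrt(17) = 2.06.

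| Test (alpha 0.05 assumed) | Power | 1 - power |
|---|---|---|
| One-sided | 0.629 | 0.371 |
| Two-sided | 0.491 | 0.509 |

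The one-sided result agrees with 0.62 to about one percentage point; the two-sided result does not. So 0.62 is the power, despite its label. The planning d enters as mean change divided by SD of change, here called dz.

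**2. Reading A: t1 mean / SD of t1 scores.** Assume an SD of 10.

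| t0 mean | t1 mean | Change / SD | t1 mean / SD |
|---|---|---|---|
| 36 | 41 | 0.5 | 4.1 |
| 50 | 50 | 0.0 | 5.0 |
| -14 | -9 | 0.5 | -0.9 |

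The third row is the first with 50 subtracted from every score. The change is the same, but the t1-only ratio moves from 4.1 to -0.9. On the raw attainment scale, a group that improved to a mean of exactly 0 (goals met on average) would have a ratio of 0. The result is therefore set by the origin of the scale and not by the effect.

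**3. Reading B: t1 mean / standard error.** This is Reading A multiplied by sqrt(17) = 4.12. In the first row, 41 / (10 / 4.12) = 16.9.

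**4. Reading C: change / standard error.** With the same numerator, dividing by SD / sqrt(n) instead of SD multiplies d by sqrt(17) = 4.12, so 0.5 would be reported as 0.5 × 4.12 = 2.06.

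**5. Reading D: change / SD of t1 scores.** With equal SDs at both times and pre-post correlation r, SD of change = SD × sqrt(2(1 - r)). Hence dz / d(t1 SD) = 1 / sqrt(2(1 - r)).

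| r (assumed) | dz / d(t1 SD) | d(t1 SD) when dz = 0.5 |
|---|---|---|
| 0.3 | 0.85 | 0.59 |
| 0.5 | 1.00 | 0.50 |
| 0.7 | 1.29 | 0.39 |
| 0.9 | 2.24 | 0.22 |

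Reading D is a legitimate measure of change, but it equals the planning quantity only at r = 0.5.

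**6. Reading E: mean / SD of the difference score that the GAS algorithm returns.** This is dz itself, and nothing would be distorted.

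**The case against.** The strongest reply is that the sentence is loose drafting and not a wrong method. It does not say that t1 is used alone. It calls the measure Cohen d, which the sample-size section ties to a pre-post comparison. Readings D and E are both sensible, and E is exactly the paired effect size. GAS is measured at every time point, so a proper standardized change can be computed whatever the sentence says. The effect size is descriptive and does not alter the test.

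Much of this stands. The wording may well be a slip, no data are at risk, and the intended quantity may be sound. But Readings D and E need words that the sentence does not contain: it mentions no change, no difference and no baseline. Nor is this a detail left to a fuller plan, since the article states a rule, and that rule conflicts with its own outcome and sample-size statement.

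A reader might go further and infer that d will be inflated about fourfold. The document does not support that. The factor of 4.1 needs the denominator to be a standard error, whereas the text says SD and nowhere mentions a standard error. It also needs the change in the numerator, which is the very element missing from the sentence. The fourfold figure and the complaint that only t1 is used therefore cannot both hold.

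A reader might also infer that a correct definition must lower the reported value. That fails under Reading D at correlations above 0.5, where dz is the larger, and under Reading E, where nothing changes.

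**Conclusion.** The point holds as a defect in the stated definition. As written, the effect size for the primary outcome names neither baseline nor change. It does not measure the pre-post effect and is not on the scale of the paired d = 0.5 used for planning. That the planning value is a paired d follows from the test named in the sample-size section. It is supported by the reproduced power of 0.629, which rests on an assumed one-sided 5% test.

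No single size can be given for the distortion. Under the literal reading it depends on the GAS scale origin: the illustrations run from -0.9 to 4.1 for the same change, and give 5.0 for no change, all with an assumed SD of 10. Under the other readings it ranges from none (E), through a factor that depends on the unknown correlation (D), to 4.1 (C). The supported conclusion is that the rule is wrong as worded and unclear in its denominator, not that the result will be inflated by a known amount.

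**What to change.** Replace the last sentence of the Analysis section with a definition that matches the paired comparison used for planning: d = mean(t1 - t0) / SD(t1 - t0) for the GAS score. Report it with a 95% CI, alongside the raw mean GAS change and its 95% CI. State that the denominator is the SD of the individual changes, so that it cannot be taken for a standard error.

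The cost is one sentence. Baseline and post-intervention GAS are already collected, and the scoring algorithm already returns the difference. The sample size and the test are unaffected. The reported d may be smaller or larger than under the current wording, depending on how that wording would have been applied and on the pre-post correlation. The definition should therefore be settled before the data are analysed.
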